## Abstract

**Background:**

Heart disease remains a leading cause of death for women in the United States. Despite this burden, awareness that heart disease is the leading cause of death among women declined from 65% in 2009 to 44% in 2019, with the largest declines observed among Hispanic, Black, and younger women. Thus, innovative, scalable, and cost-effective educational strategies are needed to improve women’s awareness of heart attack symptoms and appropriate care-seeking behaviors.

**Objective:**

This study aims to evaluate the short-term efficacy of the artificial intelligence (AI) HeartBot II, a chatbot-based educational intervention, in improving women’s awareness and knowledge of heart attack symptoms and care-seeking behavior compared with a waitlist control group.

**Methods:**

This randomized controlled clinical trial (RCT) with a waitlist control will enroll 200 women aged 25 or older, who will be randomized using a 1:1 allocation ratio. The intervention group will download the AI HeartBot II app and complete the 4 modules (including information on heart attack symptoms, risk factors, and calling 911) over 12 weeks. The waitlist control group will start receiving an identical intervention at 12 weeks. The primary outcomes will be change from baseline to 12 weeks in a 4-item heart attack response preparedness score, calculated as the mean of 4 self-reported items assessing confidence in recognizing signs and symptoms of a heart attack, distinguishing heart attack symptoms from other medical problems, calling 911 or an ambulance if a heart attack is suspected, and reaching an emergency room within 60 minutes of symptom onset. The primary analysis will estimate the intervention effect using constrained longitudinal data analysis implemented with linear mixed models, including fixed effects for time and time-by-treatment group interaction. Sensitivity analyses for the individual ordinal items will use ordinal logistic mixed-effects models.

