#### Sociodemographic and Health Risk Factors

Basic demographic information, including age, race and ethnicity, education, income, marital status, and employment status will be self-reported. Cardiovascular risk factors will also be assessed, including smoking status, current use of prescribed blood pressure, cholesterol, or diabetes medication, and family history of heart disease. These items were selected based on current clinical guidelines [36].

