#### Multiplicity and Gatekeeping Procedure

To control the family-wise error rate, a hierarchical gatekeeping procedure will be used for the primary and key secondary outcomes. First, the group-by-time interaction for the heart attack response preparedness score will be tested at a two-sided alpha level of 0.05. Only if the primary outcome is statistically significant will the four individual component items be formally tested as key secondary outcomes. *P* values for the four key secondary outcomes will be adjusted using the Holm-Bonferroni step-down procedure. All other secondary outcomes will be treated as exploratory; analyses will be descriptive or inferential, as appropriate, with nominal p-values reported without adjustment for multiplicity.

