#### Statistical Analysis

Baseline characteristics will be summarized by randomized group using counts and percentages for categorical variables and means and standard deviations for continuous variables, or medians and interquartile ranges for skewed variables. Because treatment assignment is randomized, baseline characteristics will be described primarily to assess sample comparability rather than to guide significance-based inference.

Primary efficacy analyses will compare randomized groups from baseline to 12 weeks, before the waitlist group receives the intervention. The treatment effect for the primary outcome, a 4-item heart attack response preparedness score, will be estimated using constrained longitudinal data analysis (cLDA) implemented via linear mixed models (LMMs) [37]. Consistent with the randomized design, the models will constrain the mean scores for the treatment and control groups to be equal at baseline. The primary outcome will include categorical fixed effects for time and a time-by-treatment group interaction term. The primary model contrast of interest is the coefficient for this interaction term at the 12-week follow-up, representing the baseline-adjusted between-group difference. To account for the within-subject correlation between baseline and follow-up, the cLDA models will use an unstructured covariance matrix, allowing variances and correlations to differ over time.

The 4 individual preparedness items will be analyzed as prespecified key secondary outcomes, subject to the hierarchical gatekeeping procedure described above. The primary efficacy analysis and all key secondary analyses will be based on the baseline and 12-week assessments only. Although the individual items are ordinal, the primary analysis will use the same linear cLDA framework to facilitate interpretation of mean differences and support model stability [38]. Robustness of this linear approximation will be evaluated in sensitivity analysis using ordinal logistic mixed-effects models for each individual item.

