All analyses will follow the intent-to-treat (ITT) principle, with all randomized participants in the groups to which they were assigned. Missing data will be addressed using multiple imputation by chained equations (MICE) to preserve the repeated-measures structure of the data. Multiple imputation was selected in part to address occasional missing item-level responses when constructing the composite preparedness score. Imputation will be conducted in a wide format, using predictive mean matching (PMM) so that the imputed values for the 4-point Likert items remain restricted to observed response categories. The imputation model will include treatment assignment, timepoint-specific observed item values, baseline scores, and related outcome items as predictors. The primary preparedness score will be calculated within each imputed dataset only after item-level imputation. We will generate 50 imputed datasets to reduce Monte Carlo error, and results will be combined across imputations using Rubin’s rules.

To evaluate how app engagement and module completion influence efficacy, the main ITT analyses will be supplemented by an exploratory per-protocol analysis. App engagement will be operationalized as binary module completion (completing all 4 modules vs fewer than 4 modules). In the per-protocol analysis, an unconstrained linear mixed model analogous to the primary model will be fit, restricting the intervention group to “high engagers” (participants who completed all 4 educational modules), and comparing them with the full waitlist control group. An exploratory dose-response analysis will also be conducted by examining the association between the number of completed modules (0 to 4) and the 12-week preparedness score within the intervention arm using an unconstrained linear mixed model analogous to the primary analysis. Because intervention adherence is not randomized, these analyses will be considered exploratory; the cLDA constraint of equal baseline means will not be imposed, and results will be interpreted cautiously.

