#### Power and Sample Size

This study is powered based on a total analyzed sample of n=160 (80 per group). To account for a conservative 20% attrition, we will enroll a total of 200 participants. Statistical power was estimated via Monte Carlo simulations (5000 iterations) using an empirical covariance matrix and response thresholds derived from pilot data [18]; code is provided in Multimedia Appendix 1. The simulation uses the same cLDA analysis framework described above for analysis.

For the primary outcome, the heart attack response preparedness score, the study provides 90% power to detect a raw mean difference of 0.37 points on the 1‐4 scale (Cohen *d*=0.51). This detectable effect is smaller than the within-group mean change observed in pilot data (0.78 points), although the pilot study did not include a control group [18]. For the four key secondary item-level outcomes, power was also evaluated under the prescribed hierarchical gatekeeping procedure with Holm-Bonferroni adjustment. Under this framework, the study has 90% power to detect at least one significant key secondary item for a raw difference of 0.43 (*d*=0.59). To detect significant effects across all four key secondary items (assumed to have the same effect), larger effect sizes are required; 90% power is achieved at a mean difference of 0.62 points (*d*=0.85).

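### The valid but minimal primary model and imputation model leave out baseline variables that the trial collects, so dropout protection is limited to what treatment and the preparedness items explain

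*Protocol article*

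**What the plan says.** The Abstract (Methods) says the intervention effect will be estimated "using constrained longitudinal data analysis implemented with linear mixed models, including fixed effects for time and time-by-treatment group interaction". The Statistical Analysis section describes the primary model in one line: "The primary outcome will include categorical fixed effects for time and a time-by-treatment group interaction term". It adds that "the models will constrain the mean scores for the treatment and control groups to be equal at baseline", so the baseline score is used as a constrained outcome. The four individual items are to be analysed in the same framework. No further baseline variable appears in either model.

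For missing data, the same section plans chained-equation imputation at item level with 50 datasets, and lists the predictors: "The imputation model will include treatment assignment, timepoint-specific observed item values, baseline scores, and related outcome items as predictors". No demographic or risk-factor variable is in that list.

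Such variables are nevertheless available. Under Sociodemographic and Health Risk Factors: "Basic demographic information, including age, race and ethnicity, education, income, marital status, and employment status will be self-reported". That section also covers smoking, current blood pressure, cholesterol or diabetes medication, and family history of heart disease. The Baseline section places sociodemographic characteristics in the survey completed before randomisation. The Randomization section names no stratification factor.

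On size, Power and Sample Size states that "the study provides 90% power to detect a raw mean difference of 0.37 points" (d=0.51) with 80 analysed per group, and enrols 200 to allow for 20% attrition.

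**The concern.** Two things are at stake, the second more important than the first.

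**Precision.** Prognostic baseline variables reduce residual variance at no recruitment cost. The model uses only one, the score itself.

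**Dropout.** Imputation under missing at random is only as good as the variables it conditions on. Before week 12 the intervention arm has to install an app, enter an access code, register and complete four modules of 10 to 15 minutes each. The waitlist arm only receives text messages. Dropout could therefore depend on age or education in one arm and not in the other. If such a variable also predicts preparedness, an imputation model without it carries a bias into the intention-to-treat estimate, except for whatever part the preparedness items happen to capture.

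**Working it through.** **Inputs.** From Power and Sample Size: 80 analysed per group, difference 0.37, d=0.51, power 90%, 20% attrition. From Multiplicity and Gatekeeping Procedure: the primary test "will be tested at a two-sided alpha level of 0.05". Implied SD: 0.37/0.51 = 0.725. The added R² and the dropout mechanisms below are assumptions; the document gives neither.

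**Step 1: the plan's own figures.** With no gain from baseline, the expected test statistic is 0.51 × √(80/2) = 3.226, and power is Φ(3.226 − 1.960) = 89.7% (89.4% with the noncentral t). This agrees with the stated 90%. Enrolment also agrees: 160/(1 − 0.20) = 200.

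**Step 2: gain in precision.** Start from exactly 90% at 0.37, where the expected statistic is 1.960 + 1.282 = 3.242. If covariates explain a further share R² of the residual variance:
- power = Φ(3.242/√(1 − R²) − 1.960)
- detectable difference = 0.37 × √(1 − R²)
- equivalent analysed sample = 160/(1 − R²)

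| Assumed added R² | Power at 0.37 | Difference detectable with 90% power | 160 analysed worth |
|---|---|---|---|
| 0 | 90.0% | 0.370 | 160 |
| 0.02 | 90.6% | 0.366 | 163 |
| 0.05 | 91.4% | 0.361 | 168 |
| 0.10 | 92.7% | 0.351 | 178 |

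**Step 3: dropout bias in an assumed scenario.** Take a standardised covariate that is independent of the baseline score and explains 5% or 10% of the week-12 score. Its slope is 0.725 × √0.05 = 0.162 or 0.725 × √0.10 = 0.229 points per SD. Let it drive dropout in the intervention arm only, with log-odds 0.7 or 1.0 per SD and 20% missing. Low values drop out. Among intervention responders the covariate mean then shifts by 0.130 or 0.173 SD (numerical integration over a normal covariate). An analysis without the covariate is biased by slope × shift:

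| Variance explained | Log-odds 0.7 | Log-odds 1.0 |
|---|---|---|
| 5% | 0.162 × 0.130 = 0.021 | 0.162 × 0.173 = 0.028 |
| 10% | 0.229 × 0.130 = 0.030 | 0.229 × 0.173 = 0.040 |

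That is 0.02/0.37 = 5% to 0.04/0.37 = 11% of the difference the trial is sized to detect, in the direction of overstating the effect. Simulation of 4,000 trials per scenario with 100 per arm gave the same 0.02 to 0.04 without the covariate and about zero with it. The simulation used observed-data ANCOVA as a stand-in for the two-visit constrained model, not the planned item-level imputation.

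**Step 4: do the power figures reveal how much baseline explains?** A t-test ignoring baseline needs d=0.5157 for 90% power. If d is scaled by the week-12 SD, the implied baseline-to-week-12 correlation is √(1 − (0.51/0.5157)²) = 0.15. Allowing for rounding of both d and power, the range is 0 to 0.24. But the denominator of d is not stated, and the printed item figures raise doubt about it. They imply 0.43/0.59 = 0.62/0.85 = 0.729, nearly the composite's 0.725. With Cronbach α of 0.70 the mean inter-item correlation is 0.70/(4 − 3 × 0.70) = 0.368, and a four-item mean should have √((1 + 3 × 0.368)/4) = 0.725 times the item SD. If the items have similar SDs, one value cannot be the marginal SD of both. If d was scaled by the residual SD, the correlation cannot be recovered at all.

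**The case against.** The strongest reply is that nothing here is an error. A constrained two-visit model already adjusts for the baseline outcome and is valid without more covariates. No stratification factor requires adjustment, and chance imbalance is covered by the confidence interval. Covariate sets and auxiliary variables are often settled in an analysis plan, which is not at hand. The document gives no evidence that the collected variables predict preparedness, and at an added R² of 0.02 the gain is 0.6 of a percentage point. The bias scenario is constructed, needs one-armed covariate-driven dropout, and still yields at most about 0.04 points.

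Most of this stands, and it limits the point to an improvement. It does not remove it: the article states the model terms and the list of imputation predictors, so this is a stated rule and not a silence.

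Three stronger readings are tempting and are not supported:
- **That the power figures show baseline explains almost none of the week-12 variance.** This holds only if d is scaled by the week-12 SD, which is not stated. Even then it would be a planning input from a single-arm pilot and not a property of this trial.
- **That protection against dropout bias is lost.** The planned imputation does protect against missingness explained by treatment and the preparedness items.
- **That perceived risk is a ready pre-randomisation covariate.** Its section gives no timing, and the Baseline section does not name it.

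**Conclusion.** The point holds as a low-cost improvement to a valid analysis. The primary and item-level models use no baseline predictor beyond the score, and the imputation list contains no demographic or risk-factor variable, although several are collected. Dropout protection is therefore narrower than the data allow, while 20% attrition is planned and the pre-week-12 burden differs by arm.

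The precision gain is modest: 0.6 to 2.7 percentage points of power for an assumed added R² of 0.02 to 0.10, and nil if the covariates are not predictive. The bias removed is about 0.02 to 0.04 points under the assumed one-armed dropout mechanism. It would be smaller if the covariate is correlated with the baseline items, and zero if dropout does not depend on it. None of these assumptions can be checked against the document. The case for acting rests on the very low cost and on timing.

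**What to change.** Before anyone sees outcomes by arm:

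1. Prespecify a short set of baseline variables, for example age, education, family history of heart disease and current cardiovascular medication. Confirm that each is recorded in the survey completed before randomisation.
2. Add them to the imputation model. This is the step that addresses dropout bias.
3. Include the same variables, each with its interaction with time, in the constrained model for the score and the four items. A main effect alone would force the same effect at both visits. Keep the equal-baseline constraint.
4. Retain the model without covariates as a sensitivity analysis.
5. In Power and Sample Size, state which SD scales d and the baseline-to-week-12 correlation used in the simulation.

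The cost is a few sentences in the analysis plan and a few degrees of freedom. No new data collection is needed if step 1 confirms the timing. The downside is no gain if the chosen variables prove weak. Choosing them after outcomes by arm are known would not be credible; analysis is planned for spring 2027, so there is time.

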**Results:**

We received approval from the University of California, San Francisco, Institutional Review Board (No. 25‐44825) on January 9, 2026, and this trial was registered on ClinicalTrials.gov (NCT07416734) on February 11, 2026, prior to enrollment of the first participant. Recruitment began in April 2026. As of manuscript submission, 86 participants were enrolled. Enrollment is expected to be completed by September 2026, and all follow-up assessments are anticipated to be completed by March 2027. Data analysis is expected to begin in spring 2027, with study results anticipated for publication later in 2027.

**Conclusions:**

To the best of our knowledge, this is the first RCT to rigorously evaluate the efficacy of the AI HeartBot II intervention. If effective, AI HeartBot II could provide a scalable, accessible, and cost-effective public health communication strategy to improve women’s awareness of heart attack symptoms and promote timely care-seeking behaviors in the United States.

## Introduction

Artificial intelligence (AI) chatbots are computer programs designed to simulate human conversations via text, speech, or both. Early rule-based AI chatbots relied on scripted dialogue flows. However, recent advancements in natural language processing (NLP) and large language models (LLMs) have significantly expanded the capabilities of AI chatbots, such as having more flexible and human-like naturalistic conversations as well as an understanding of more complex user input. Furthermore, AI chatbots can provide personalized, scalable, round-the-clock communication, making them attractive tools for health care and research. Given such advantages, AI chatbots have been rapidly developed and adapted to enhance patient education, counseling, clinical decision-making, and health management efficiency. Recent systematic reviews and meta-analyses on AI chatbots have shown potential to improve mental health [1-3] and other chronic illnesses [4] and to promote healthy lifestyles and self-care behaviors [5-10].

Despite these advancements, the use of AI chatbots, especially those powered by LLMs, in the area of cardiovascular health education remains underexplored. Heart disease remains the number one cause of death for women in the United States [11], with over 60 million women affected [12]. Public health campaigns, such as “Go Red for Women” [13] by the American Heart Association (AHA), have aimed to raise awareness over the past two decades. However, awareness that heart disease is the leading cause of death among women declined from 65% in 2009 to 44% in 2019 [14], with the steepest declines observed in Hispanic, Black, and younger women [15-17]. Therefore, an urgent need exists for a novel approach to increase awareness and knowledge of heart disease in women [18,19].

To address this gap, we conducted a series of studies to evaluate the feasibility, acceptability, and potential efficacy of an AI chatbot (hereafter referred to as “HeartBot I”) in increasing women’s awareness and knowledge of heart attack symptoms and appropriate care-seeking behavior. The results of those studies and HeartBot I design details were published elsewhere [18,19]. In brief, HeartBot I was feasible (ie, no withdrawal from HeartBot I conversation) and accepted by women, and its interactions were significantly associated with improvements in awareness and knowledge of all heart attack outcomes. However, since HeartBot I was a rule-based chatbot, its behavior and responses were limited to content authored specifically for HeartBot I conversations. To improve HeartBot I’s capacity, we incorporated all women’s heart attack and relevant questions collected in our previous studies and expanded its knowledge bank to enable more educational conversations. To achieve more human-like, natural, and personalized conversations, we implemented a new version of AI HeartBot (hereafter referred to as “HeartBot II”) powered by an LLM, specifically gemini-2.5-flash [20] through the Google Conversational Agents platform [21]. Combined with the high prevalence of smartphone ownership [22], an LLM-based HeartBot II could have significant advantages over traditional public health campaigns. This study aims to evaluate the efficacy of the HeartBot II program, as compared to the waitlist control, in increasing women’s awareness and knowledge of heart attacks. The waitlist control group will start interacting with HeartBot II after 12 weeks and will receive an SMS text message once a week from the research team for the initial 12 weeks for attention control. This protocol outlines the design and methodology of the upcoming randomized controlled trial (RCT) with a waitlist control to assess the efficacy of an LLM-based HeartBot II in this context.

## Methods

### Study Design

An RCT with a waitlist control is being conducted to compare the efficacy of HeartBot II, as compared to the waitlist control, in increasing awareness and knowledge of heart attacks in women. Figure 1 shows the study design. This study was registered with ClinicalTrials.gov (NCT07416734) on February 11, 2026. All study procedures will be done online remotely.

**Figure 1. F1:**
[figure not shown]
Study flow diagram and assessment schedule for the AI HeartBot II randomized controlled trial. AI: artificial intelligence.

### Ethical Considerations

This study was funded by the University of California, San Francisco (UCSF), Resource Allocation Program in February 2025. Correspondence from the peer review process associated with this funding award is provided in Peer Review Report 1. The study protocol was approved by the UCSF Institutional Review Board on January 9, 2026 (IRB number 25‐44825). This study was also registered with ClinicalTrials.gov (NCT07416734) on February 11, 2026. The SPIRIT (Standard Protocol Items: Recommendations for Interventional Trials) 2025 checklist of items to address in a randomized trial protocol is attached in Checklist 1.

